### Quality of Life

Patients will receive QoL forms before start of hormonal treatment, at end of radiotherapy and at follow-up time points 6 months, 1, 2, 3 year and 5 years. PCSS form, a validated form of symptom evaluation will be used

## **Withdrawal from treatment**

The patient can at any time withdraw from treatment. The date and reason for withdrawal should be reported in the CRF. If a patient is lost to follow up the date and reason for this should be reported in the CRF. Loss of follow-up does not mean that the patient leaves the study. All patients that are randomised should be followed until the end points have been reached - irrespective of further treatment regimes and in accordance with the intention of treatment strategy.

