## **Dose escalation with SIB to intraprostatic/lymphatic GTV in high risk prostate cancer**

### ***Method***

#### **Study design**

The present study will be performed as a single institute prospective consecutive phase II clinical trial with matched historical controls of dose escalation to intra prostatic tumor and, if eligible, to radiological lymph node metastasis in the pelvis.

Patients are recruited consecutively during their consultation at Cancer Centre, Umeå University Hospital, after given both oral and written patient information and due time for consideration.

All patients included in the present study will receive external radiotherapy (RT) of 2,2 Gy to 77 Gy to the prostate in 35 fractions and pelvic nodal radiotherapy of 1,6 Gy to 56 Gy in 35 fractions. A simultaneous integrated boost (SIB) of 84 Gy in 35 fractions (fractional dose 2,4 Gy) will in addition be delivered to macroscopic tumor in the prostate. In case of radiological suspected metastasis in one or more of the pelvic lymphatic nodes according to PET/CT-scan an additional SIB of 70 Gy in 35 fractions (fractional dose 2 Gy) will be delivered to PET-positive nodules.

At baseline QoL questionnaire and baseline symptoms will be collected after given informed consent. Renewed QoL and symptom scoring will be collected at end of treatment and during follow up. A historical control group of 100 consecutive patients receiving external radiotherapy to prostate/pelvic lymph nodes without dose escalation to the intra prostatic macroscopic tumor will be used to compare PFS, OS, LC and QoL. Matching criteria is T-stadium, pre-treatment PSA and GS.

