### ***Patients***

86 consecutive patients with high risk prostate cancer at Cancer Centre, Umeå University Hospital planned for external radiotherapy with curative intent that meets the following inclusion criteria and none of the exclusion criteria:

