### **Exclusion:**

- Non MR-safe implants or other contraindication to MRI
- WHO PS>1
- Previous pelvic irradiation
- TURP within 6 months
- IPSS >19
- Metastatic disease in skeleton, parenchymal organs or lymph nodes outside the pelvis
- Kreatinin clearance < 30ml/min according to  
<http://www.fass.se/LIF/produktfakta/kreatinin.jsp>

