### *Functional imaging*

In case of inclusion in the full protocol, patients will be referred to an 11C-acetate PET/MRI in treatment position before onset of neo adjuvant hormonal treatment. Three additional 11C-acetate PET/MRI will be performed; after implantation of fiducial markers, in mid-treatment and six months after end of RT. For patients not included in the parallel prognostic imaging protocol, MRI before hormonal treatment and after implantation of the fiducial markers will be performed for target definition. The slice thickness in the planning treatment series is 2 mm.

For all patients, anatomical series consisting of T2 weighted spin-echo based sequences, a T1 weighted gradient echo sequence with DIXON type fat/water separation and a MR angiography. The functional MRI scans include a diffusion weighted EPI sequence (DWI) and a dynamic contrast enhanced spoiled gradient echo sequence (DCE). The DWI sequence is run using two multiple b-values and is reconstructed to an apparent diffusion coefficient (ADC) map that is used for target delineation. The DCE images are analysed using kinetic models and reconstructed to the parameter images used for target definition. The angiography images are registered to the CT image using a rigid mutual information algorithm. All other MRI series are registered to the CT image set using a landmark registration algorithm, with landmarks defined by the implanted gold fiducial markers visible in the T1 weighted MR image and CT. The anatomical series will be used for target delineation in combination with the primary PET scan and planning CT. The primary DWI, will be used in combination with the PET scans to define a macroscopic intra prostatic tumor volume.

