### ***Statistical procedures***

### **Power considerations**

In this extremely high risk population there is a considerable risk of relapse. Calculating on an improvement of 20% with dose-escalation and irradiation of lymph-nodes with boost to radiologically pathologic nodes we would need 86 patients to detect an increased freedom from relapse at three years with 80 % power and a two-sided significance level of 0,05.

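### Trial patients enter when planned for radiotherapy but historical controls only if they received it, so failures before radiotherapy can count on the trial side only

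*Protocol*

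**What the plan says.** **Trial group.** The Patients section takes 86 consecutive patients "planned for external radiotherapy with curative intent", so entry is by plan. The Flowchart ticks inclusion and consent in the column for three months before radiotherapy, and Concomitant therapy puts three months of hormonal treatment ahead of it. The primary endpoint, PFS, is timed from inclusion. Withdrawal from treatment lets a patient withdraw at any time, yet requires follow-up to the endpoints "irrespective of further treatment regimes and in accordance with the intention of treatment strategy".

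**Control group.** Study design describes "A historical control group of 100 consecutive patients receiving external radiotherapy to prostate/pelvic lymph nodes without dose escalation" to the intraprostatic tumour. This group is to be used for PFS, overall survival, local control and quality of life. Matching is on T stage, pre-treatment PSA and Gleason score. No start date is given for controls.

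**Imaging.** Functional imaging states (last word omitted here): "In case of inclusion in the full protocol, patients will be referred to an 11C-acetate PET/MRI in treatment position before onset of neo adjuvant hormonal". Patients outside the parallel imaging protocol have MRI for target definition instead. The exclusion criteria include "Metastatic disease in skeleton, parenchymal organs or lymph nodes outside the pelvis".

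**The concern.** With historical controls, comparability rests entirely on how the two groups are selected. Here one group is selected by intention, about three months before radiotherapy, and the other by having reached it. A trial patient who dies, progresses or withdraws during the hormonal run-in stays under follow-up with a clock already running. A past patient with the same course did not receive radiotherapy and so does not meet the control description. Matching on T stage, PSA and Gleason score does not correct this.

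Moving the start date alone does not repair it either. If both clocks start at hormonal treatment, controls still cannot fail before radiotherapy. If both start at radiotherapy, trial patients who never had it have no start date. At stake is a small systematic shift in the PFS and overall survival comparisons.

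**Working it through.** **1. The plan's own figure.** Power considerations gives "80 % power and a two-sided significance level of 0,05". It also states "Calculating on an improvement of 20% with dose-escalation" and "we would need 86 patients to detect an increased freedom from relapse at three years". It gives no control rate and does not say whether the 20% is absolute or relative, so 86 cannot be derived from the stated inputs alone. Read as 20 absolute points, the pooled two-proportion formula gives 86 per group at 57% versus 77%, or at 63% versus 83% with continuity correction. The figure is thus attainable, and nothing below depends on it.

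**2. Inputs for the illustration.**
- From the protocol: 86 trial patients, 100 controls, two-sided 0.05, a 20% improvement (taken as 20 points).
- Assumed: three-year control rate p0 of 50% or 60%; k = 2, 4 or 6 of 86 included patients (2.3%, 4.7%, 7.0%) never start radiotherapy.

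**3. Formulas.** With p1 = p0 + 0.20 among irradiated trial patients, the observed trial rate is
- all k fail: p1 × (1 − k/86);
- the k do as well as controls: p1 × (1 − k/86) + p0 × k/86.

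Power = Φ[(d − 1.96 × SE0)/SE1], where d is the observed difference, SE0 uses the pooled rate and SE1 the separate rates.

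**4. One case in full (p0 = 0.50, k = 2, both fail).** Trial rate = 0.70 × 84/86 = 0.684, so d = 0.184. Pooled rate = (50 + 58.8)/186 = 0.585. SE0 = √[0.585 × 0.415 × (1/100 + 1/86)] = 0.0725. SE1 = √[0.25/100 + 0.684 × 0.316/86] = 0.0708. Power = Φ[(0.184 − 0.142)/0.0708] = Φ(0.59) = 0.72.

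**5. Results (control rate 50% / 60%).**

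| k | Difference, all fail (points) | Power | Difference, as controls (points) | Power |
|---|---|---|---|---|
| 0 | 20.0 / 20.0 | 0.80 / 0.85 | 20.0 / 20.0 | 0.80 / 0.85 |
| 2 | 18.4 / 18.1 | 0.72 / 0.76 | 19.5 / 19.5 | 0.78 / 0.83 |
| 4 | 16.7 / 16.3 | 0.64 / 0.66 | 19.1 / 19.1 | 0.76 / 0.81 |
| 6 | 15.1 / 14.4 | 0.55 / 0.55 | 18.6 / 18.6 | 0.73 / 0.79 |

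**6. With no true effect,** the all-fail case shifts the difference by −p0 × k/86. That is −1.2 to −1.4 points for k = 2 and −3.5 to −4.2 points for k = 6.

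**7. The clock.** Because controls have no stated start, the two clocks could differ by three months. Under a constant hazard this changes a 36-month rate of 60% to 0.60^(33/36) = 62.6% or 0.60^(39/36) = 57.5%, about 2.5 points either way. The remedy therefore needs a common time zero as well as a common entry condition.

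**The case against.** Four objections carry weight.

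*No analysis set is defined.* The intention-of-treatment sentence is a follow-up rule under Withdrawal from treatment. It speaks of randomised patients although nobody is randomised, and analysis sets may be left to an SAP that is not shown. This stands: a reader might infer that the protocol prescribes an intention-to-treat analysis of the trial group, and it does not say so. The mismatch survives without that sentence, because entry by plan and a PFS clock from inclusion are fixed elsewhere in the protocol.

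*The control phrase may only describe the regimen.* Study design also says that all included trial patients will receive radiotherapy. That states the planned treatment, and the withdrawal section foresees departures from it. For controls, receipt of radiotherapy is the only entry condition written down.

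*The scan does not clearly follow inclusion.* A reader might infer that all trial patients are included before a staging scan. The documents do not support this. The PET/MRI sentence covers full-protocol patients only, and the first scan shares the flowchart column with inclusion. Implanted markers are an inclusion criterion, yet Functional imaging lists the scan after implantation as an additional one, later than the first. A patient with metastases outside the pelvis could be a screen failure. The point therefore rests on the run-in and not on the scan.

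*The direction is not fixed.* A reader might infer a certain bias against the boost. Failures before radiotherapy do push that way. Removing full-protocol patients upstaged by PET/MRI would push the other way, since the documents do not say that controls had PET.

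**Conclusion.** The point holds as a mismatch of entry condition and time zero. Trial patients are taken from the plan to irradiate and timed from inclusion; controls are taken from receipt of radiotherapy with no stated start. Nothing else in the protocol reconciles the two.

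The run-in part tends to work against the boost; the net direction is uncertain. The size is unknown and probably small: about 0.5 to 2 points for two patients never irradiated, depending on how they fare. The fall to about 55% power needs six such patients who all fail by three years, an upper bound within the assumed range. It should not be read as showing that the trial is underpowered. All these figures rest on an assumed control rate of 50–60%, a 20-point absolute gain and an assumed number never irradiated, none of which the protocol states in that form. The change is worth making because the rule can be settled cheaply before outcomes are compared.

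**What to change.** For the comparison with historical controls, state one entry condition and one time zero for both groups:

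- Primary comparison: trial patients who started the study radiotherapy against controls who started theirs, both timed from the start of radiotherapy.
- List every included patient who never started radiotherapy, with the reason, and identify any removed because of PET/MRI findings.
- Report the all-included analysis, timed from inclusion, as a sensitivity analysis beside the primary one.
- Keep the follow-up duty in Withdrawal from treatment for all included patients.

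The cost is a change of text, including the start date in the PFS definition as used for this comparison; treatment is untouched. The downside is that a few included patients leave the primary comparison. Because removal on PET findings could favour the boost, the sensitivity analysis must always be shown with it. Identifying controls at the treatment decision instead would keep the clock from inclusion, but it requires past records of patients who were planned for radiotherapy and did not receive it.

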## **Flow Chart**

See App 1

## **Side effects**

Side effects should be reported according to GCP and noted in the CRF. Symptoms related to proven tumour progression should not be considered as side effects. Grading will be done according to RTOG radiotherapy scoring system. For events except bladder and small/large intestinal we will use Common Terminology Criteria for Adverse Events (CTC-AE) version 4.1.

### *Adverse Events (AE)*

Reported in CRF.

### *Serious Adverse Events (SAE)*

Serious side effects during the study should be reported to Klinisk Forskningsenhet, KFE, Norrlands universitetssjukhus. Hospitalisation due to suspected **serious side effects related to treatment** should be reported within 10 days to Klinisk Forskningsenhet, by FAX. Symptoms and death related to proven tumour progression should not be considered as serious side effects. Serious side effects are those that are life-threatening, or may give serious permanent damage or dysfunction of a magnitude that need hospital care. Grading will be done according to RTOG/EORTC. For events except bladder and small/large intestinal use Common Terminology Criteria for Adverse Events (CTC-AE) version 4.1.

## ***Data management and clinical procedures***

### **Case Record Form (CRF)**

A paper version will be used.

### **Data management**

KFE

### ***Statistical procedures***

### **Power considerations**

In this extremely high risk population there is a considerable risk of relapse. Calculating on an improvement of 20% with dose-escalation and irradiation of lymph-nodes with boost to radiologically pathologic nodes we would need 86 patients to detect an increased freedom from relapse at three years with 80 % power and a two-sided significance level of 0,05.

## **Statistical methods**

Prospective phase II clinical trial with matched historical controls.

## ***Report and communication of results***

### **Publication**

All presentations of data from the study, in the form of lectures or publications, should only be made after agreement with the study-coordinators. The results of the study will be submitted to an internationally recognized medical journal. It is the intention of the present study that analysis of the primary endpoint should not be made until the required number of events has been obtained. If solid statistical data emerge, or other exceptional circumstances occur they may, however, be published earlier after approval by the study-coordinators.

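### The Publication section allows early release of primary-endpoint results once they look convincing, with no interim rule to protect the 0.05 level, and its event trigger does not match the three-year power basis

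*Protocol*

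**What the plan says.** Power considerations sizes the trial in patients for a fixed time point: "we would need 86 patients to detect an increased freedom from relapse at three years", "with 80 % power and a two-sided significance level of 0,05". The effect is given as "Calculating on an improvement of 20% with dose-escalation", without saying whether the 20% is absolute or relative. The control rate is described only in words ("there is a considerable risk of relapse"). No hazard ratio or event count appears.

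Publication sets the timing differently. The intention is that "analysis of the primary endpoint should not be made until the required number of events has been obtained". The next sentence relaxes this: "If solid statistical data emerge, or other exceptional circumstances occur they may, however, be published earlier", with the study-coordinators' approval as the only condition.

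Three other places bear on the point:
- Study design names a historical control group of 100 patients.
- Primary endpoint measures PFS from inclusion. It requires a PSA rise to be confirmed on three measurements at least a month apart. During the first 24 months after treatment it lets the physician hold back a PSA progression because of possible bounce and correct the date afterwards.
- Trial period gives 18 months of recruitment and 60 months of follow-up, and ties neither to an analysis.

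**The concern.** There are two problems.

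First, the release clause makes publication depend on how the efficacy data look. To judge that the data are solid, someone must examine accumulating results. With no boundary, number of looks or adjusted level stated, each such examination is another chance to cross 0.05, and results released because they look good tend to overstate the effect. PFS is especially fragile when read early, because progressions inside the bounce window may still be withheld or re-dated.

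Second, a sample size built on a three-year comparison implies analysis when patients have been followed for three years. A trigger counted in events can fall at another time, and the protocol does not say whether events in the historical controls count towards it.

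**Working it through.** **1. The plan's own figure.** The control rate is missing, so 86 can only be tested for plausibility. Take an absolute gain of 20 points, 100 controls, 86 treated, and 50% against 70% (assumed). The pooled rate is (100×0.50 + 86×0.70)/186 = 0.5925.
- SE under the null: √[0.5925×0.4075×(1/100 + 1/86)] = 0.0723
- SE under the alternative: √[0.25/100 + 0.21/86] = 0.0703
- Power: Φ[(0.20 − 1.96×0.0723)/0.0703] = 79.7%

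So 86 is plausible as a fixed-time comparison of two proportions. No event number follows from it.

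**2. Event target implied by the same effect.** Under proportional hazards, HR = ln(p + 0.20)/ln(p), where p is the three-year control rate. Schoenfeld's formula gives d = (1.960 + 0.842)² / [(86/186)(100/186)(ln HR)²] = 31.57/(ln HR)². Events expected once everyone has three years are 100(1 − p) + 86(0.80 − p). The control rates are assumptions.

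| Three-year rates | HR | Events needed | Expected, controls | Expected, treated | Expected, total |
|---|---|---|---|---|---|
| 30% vs 50% | 0.576 | 103.6 (104) | 70 | 43.0 | 113.0 |
| 40% vs 60% | 0.557 | 92.5 (93) | 60 | 34.4 | 94.4 |
| 50% vs 70% | 0.515 | 71.5 (72) | 50 | 25.8 | 75.8 |
| 60% vs 80% | 0.437 | 46.0 (47) | 40 | 17.2 | 57.2 |
| 70% vs 90% | 0.295 | 21.2 (22) | 30 | 8.6 | 38.6 |

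In every row the target is below the total expected at three years. At 40% the two nearly coincide. At 60% the target is 10 events short of the three-year total, and at 70% about 17 short. If control events count and the controls already have three years of follow-up (both assumptions), the controls alone supply 40 of 47 events at 60%. At 70% their 30 events exceed the target before any treated patient has progressed.

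**3. Type I error if the release clause is used.** The number of looks is an assumption. Looks are equally spaced, and each declares success if |z| > 1.96. There are two cases, both simulated under the null with a normal approximation:
- *Controls complete:* z at look k is (mean of the nₖ treated − mean of the 100 controls)/√(1/nₖ + 1/100), in standardised units, with nₖ rising to 86. The same control mean enters every look, so successive z-values are more strongly correlated.
- *Both groups accruing together:* the usual independent-increments path.

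| Looks in total | Controls complete | Both accruing |
|---|---|---|
| 1 | 5.0% | 5.0% |
| 2 | 7.8% | 8.3% |
| 3 | 9.7% | 10.7% |
| 5 | 12.7% | 14.2% |

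**4. Timing of a three-year analysis.** The flowchart puts inclusion about 3 months before radiotherapy, and 35 fractions at 5 a week take 7 weeks (about 1.6 months). The bounce window therefore closes about 3 + 1.6 + 24 = 28.6 months after inclusion, before the three-year point. The local-control biopsy, 36 months after the end of radiotherapy, falls about 3 + 1.6 + 36 = 40.6 months after inclusion, beyond it.

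**The case against.** The strongest reply is that an event target, interim boundaries and alpha handling commonly sit in a statistical analysis plan, which is not at hand. That stands for the missing event number: its absence from the protocol is not itself a fault. It does not rescue the release clause, which the protocol itself states and which an analysis plan would have to contradict.

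A reader might infer that the event trigger and the three-year basis conflict. The documents do not show this. A trial can be sized on a three-year rate and still wait for events on a time-to-event endpoint, and at control rates of 40% to 50% the two nearly coincide. What can be said is that they rest on different bases and need not agree.

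A reader might also infer that the type I error is uncontrolled, or that the coordinators are watching the results and testing at the full 0.05. The text says neither. It states an intention not to analyse early and then allows an exception. The inflation arises only if the exception is used for efficacy. The higher set of percentages also assumes that both groups accrue together, and with complete historical controls the lower set applies.

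Finally, exceptional circumstances may properly include safety, and this is a phase II study with historical controls. Both temper the weight of the point without removing it.

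**Conclusion.** The point holds in a limited form. The Publication section contains a data-dependent release rule with no statistical safeguard, so "a two-sided significance level of 0,05" is not protected if that rule is used for efficacy. With two to five looks the error would be about 8% to 13% against complete controls, or 8% to 14% if both groups accrue together. These figures illustrate the risk; they do not estimate what the trial will do, since the number and spacing of looks are assumed.

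The event trigger does not match the power basis. Its implied size, about 21 to 104, depends on an unstated control rate, an absolute reading of the 20% and proportional hazards. It may be met before all patients have three years of follow-up, mainly at control rates of 60% or more.

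**What to change.** In Publication, replace the event trigger with a single primary PFS analysis when the last included patient has three years of follow-up from inclusion and the confirmatory PSA measurements are available. Analyse local control separately, when the last biopsy at 36 months after radiotherapy is in, because it falls due after the PFS date. Describe follow-up from there to 60 months as descriptive, with no new primary test.

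For efficacy, delete the early-release clause. If early release is wanted, replace it with a prespecified interim look that has a stated time and an alpha-spending boundary. Keep early reporting of safety.

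The change is a few sentences. What is lost is the freedom to publish efficacy early at the coordinators' discretion.
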